The iliac crest holds a reservoir of spongious bone that is frequently used as a source of bone autograft, providing extracellular matrix (for osteoconduction), growth factors (modulating bone healing as per osteoinduction), and patient's cells (leading to local osteogenesis). However, major complications in 5% of the cases have been reported, including donor defect hernias, vascular injuries, sciatic nerve injury, deep infection, deep haematoma requiring transfusion, and iliac wing fracture. Minor related complications include pain at the extraction site in 5% cases, superficial haematoma or seroma or superficial infection at the extraction site in 13% cases, and ilioinguinal neuralgia in 2% cases [7]. Other limitations of iliac crest autograft (ICA) fostering research for alternatives include limited amount of available bone (particularly if previous harvesting and replacement by fibrous tissue) and limited efficacy. Although a benchmark, insufficient information about iliac crest autograft efficacy is available from the literature. When used as a control, a recent multicentric trial with 61 patients treated with autograft observed 74% radiological consolidation (45/61) by rigorous criteria (bridging in at least three of four views) at 9 months, even if only 25% of these cases were atrophic nonunions [8].

Culture-expanded autologous MSCs combined with biomaterial granules as carrier agents have been proposed as a promising technology to substitute bone autograft to augment nonunions in early feasibility studies [9, 10]. However, studies and publications vary regarding the origin of MSCs, the expansion protocol, the reproducibility and variability of the cell product, the quality of this cell product at delivery, the demographics of the treated patients, the diagnostic criteria of nonunion in the inclusion criteria, the bone healing criteria, the safety reporting, and the follow-up. Most importantly, the confirmed dose in the implanted cell product is unclear, and previous trials just declare to implant the maximum cell dose that can be generated by the available technology at the facility producing the cell expansion.

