### 2.2. Study Objectives

The primary objective is to determine if the combined treatment of the ATMP, *hBM-MSC + biomaterial (G2)*, is superior to the control, *iliac crest autologous graft (G1)*, to obtain radiological and clinical bone consolidation at 12 months after surgery of diaphyseal and/or metaphysodiaphyseal (femur, tibia, and humerus) atrophic or oligotrophic nonunions after a fracture (more than 9 months after the acute fracture and insufficient bone bridging to stabilize the fracture, insufficient bone biological activity in the fracture, and failure of previous treatments). The secondary objectives (SO) are the following: (SO1) to determine if the *low dose of hBM-MSC + biomaterial (G2b)* is noninferior to the *high dose of hBM-MSC + biomaterial (G2a)* to obtain radiological consolidation at 12 months after surgery of diaphyseal and/or metaphysodiaphyseal (femur, tibia, and humerus) nonunions after an unhealed fracture; (SO2) to compare the percentage of bone consolidation between the G1 and G2 treatment arms at 6 and 24 months after surgery and between the G2a and G2b treatment arms at 6, 12, and 24 months after surgery; (SO3) to compare the radiological consolidation between the G1 and G2 treatment arms and between G2a and G2b treatment arms, at baseline and 6, 12, and 24 months after surgery; (SO4) to compare pain with and without weight bearing using the Numeric Rating Scale (from 0 to 10) between the G1 and G2 treatment arms and between G2a and G2b treatment arms, at baseline and 6, 12, and 24 months after surgery; (SO5) to compare the rate of further surgical intervention at the callus site between the G1 and G2 treatment arms and between G2a and G2b treatment arms at 6, 12, and 24 months after surgery; (SO6) to compare the early and global complication rate between the G1 and G2 treatment arms and between G2a and G2b treatment arms at 6, 12, and 24 months after surgery; (SO7) to assess the safety of autologous hBM-MSCs between the G1 and G2 treatment arms at 6, 12, and 24 months after surgery; (SO8) to identify the factors associated with bone consolidation between the G1 and G2 treatment arms and between G2a and G2b treatment arms at 6, 12, and 24 months after surgery; and (SO9) to compare the physical and mental health status using the SF-36 Health Survey at baseline and 6, 12, and 24 months after surgery. Outcome measures are described in Table 1.

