### 2.4. Treatments

The active comparator treatment (augmentation with spongious ICA) is a surgical procedure considered the standard of care, which requires the extraction of the needed spongious bone graft from the iliac crest at nonunion surgery. The experimental treatment (augmentation with autologous hBM-MSCs combined with the previously described CE-marked biphasic bioceramic) includes expansion of MSCs under GMP conditions in associated facilities. For both experimental arms (G2a and G2b), expanded autologous hBM-MSCs will be mixed in the surgical setting, immediately before implantation, with the previously described biomaterial called MBCP+, a class III, CE-marked, and FDA-approved biomaterial, provided by Biomatlante (Nantes, France) in a syringe ready to use.  Table 3 summarizes the study arms.

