### 3.2. Plan of Analysis

Primary and secondary endpoints and the statistical plan of analysis are described in Table 1. Five subgroups for analysis are declared: manufacturing site (Spain, France S1, France S2, Germany, and Italy); anatomical site: femur, humerus, and tibia; time (months) since acute fracture; smoking habits (yes/no); and sex (female/male). For these, Fisher's exact test for categorical variables, *t*-test or one-way ANOVA for Gaussian distributed variables, Mann–Whitney test and Kruskal-Wallis for non-Gaussian continuous variables will be used.

The plan of analysis will be tested in the following two populations of analysis: (a) modified full analysis set (mFAS) that will include all patients who have received treatment; (b) per protocol population (PP) that will include those patients in the mFAS set without major protocol deviations. Procedures to account for missing or spurious data will include patients whose information on consolidation is unknown at the end of the trial and will be considered failures, irrespectively, to the drop-out reason. With regard to the radiological consolidation, the baseline value will be used to impute the missing case; in case of treatment-related missing data, the missing case is not imputed otherwise. No formal imputations will be performed for the rest of variables, and the analyses will be based on the Available Data Only (ADO) approach.

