SO4: to compare pain with and without weight bearing using the G1 versus G2 and G2a versus G2b treatment arms	Pain score using the Numeric Rating Scale from 0 to 10, when 0 = no pain at all and 10 = worst pain ever	At baseline and 6, 12, and 24 months after surgery	Fisher's exact test Mann–Whitney test

SO5: to compare the rate of further surgical intervention at the callus site between G1 versus G2 and G2a versus G2b treatment arms	Further surgical intervention at the callus site is considered when nail replacement, plate replacement, or replacement of all components of the previous surgery are performed.	At 6, 12, and 24 months after surgery	Fisher's exact test

SO6: to compare the early and global complication rate between G1 versus G2 and G2a versus G2b treatment arms	Early (<3 months) and global complications included the following: (i) AE related to the product application process (surgical or other, including BM or ICA harvesting) (ii) Local heterotopic ossification (iii) Local bone resorption (iv) Local osteolysis (v) Local and general infection (vi) Vascular problems (ischemia, phlebitis) (vii) Neurological problems (viii) Unexpected events (e.g., hypersensitivity, immunological, and toxic) (ix) AE related to concomitant medication (e.g., anaesthetics)	At 6, 12, and 24 months after surgery	Fisher's exact test

SO7: to assess the safety of autologous hBM-MSCs between the G1 and G2 treatment arms	Safety understood as early or global complication rates and SAE rates, related to the use of hBM-MSCs	At 6, 12, and 24 months after surgery	Fisher's exact test

SO8: to identify the factors associated with bone regeneration between G1 versus G2 and G2a versus G2b treatment arms	Association outcomes (*β*, RR)	At 6, 12, and 24 months after surgery	Log-binomial regression model and mix model for repeated measurements^∗∗^

SO9: to compare the physical and mental health status between G1 versus G2 and G2a versus G2b treatment arms	SF-36 Health Survey score	At baseline and 6, 12, and 24 months after surgery	*t*-test or Mann–Whitney test

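### SO7 tests SAEs related to hBM-MSCs against an arm that receives no cells, so no row of Table 1 gives a valid between-arm comparison of SAEs

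*Protocol article*

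**What the plan says.** Section 2.2 sets SO7 as "to assess the safety of autologous hBM-MSCs between the G1 and G2 treatment arms at 6, 12, and 24 months after surgery". Unlike SO2 to SO6 and SO8, it lists no G2a versus G2b contrast. The SO7 row of Table 1 repeats the G1 versus G2 contrast, names Fisher's exact test, and defines the outcome as "Safety understood as early or global complication rates and SAE rates, related to the use of hBM-MSCs".

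Section 2.4 describes the arms. On the control: "The active comparator treatment (augmentation with spongious ICA) is a surgical procedure considered the standard of care". On the cells: "For both experimental arms (G2a and G2b), expanded autologous hBM-MSCs will be mixed in the surgical setting". Table 3 agrees: G1 is autograft alone, and only G2A and G2B contain expanded cells.

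The SO6 row of Table 1 covers early and global complications. It lists, among others, harvest-related adverse events of either procedure, infection, vascular and neurological problems, and unexpected events. It compares G1 with G2 and G2a with G2b by Fisher's exact test and does not restrict events to those attributed to the cells.

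**The concern.** The SO7 outcome is conditioned on an exposure that only one of the two compared arms has. A G1 patient treated as allocated cannot have an event related to hBM-MSCs, whatever happens to that patient. The comparison is then a count in G2 set against a structural zero.

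Two misreadings follow. A non-significant SO7 could be reported as no safety difference, although the control could not contribute an event. A significant SO7 would show only that the cells cause some events, which needs no control arm. In neither case does a serious harm of autograft enter the SO7 comparison. For SAEs as a class, the reader of the trial would not learn whether one strategy produces more than the other.

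**Working it through.** **1. Inputs.** Arm sizes are 36 (G1) and 72 (G2), from Section 3.1.1. The test is Fisher's exact, from Table 1. The article gives no expected rate, alpha or power for SO7, so there is no stated figure to reproduce. I use two-sided 5%. The G2 event rates in step 4 are assumptions.

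**2. The structural zero.** The outcome requires relatedness to hBM-MSCs (Table 1). G1 contains no hBM-MSCs (Section 2.4, Table 3). The G1 count is therefore 0/36 by definition.

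**3. What the test does.** Given x events in total, all in G2, the probability of the observed table is C(72,x)/C(108,x). The two-sided p-value adds every table that is no more likely.

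- x=7: observed table 0.0528. Tables with 5, 6 or 7 events in G1 add 0.0346 + 0.0050 + 0.0003 = 0.0399. p = 0.0927.
- x=8: observed table 0.0340. Tables with 6, 7 or 8 events in G1 add 0.0141 + 0.0017 + 0.0001 = 0.0159. p = 0.0499.
- x=9: observed table 0.0218, and the other tail adds 0.0060. p = 0.0278.
- Smaller counts: 1/72 gives p = 1.00 and 4/72 gives p = 0.30.

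The reference distribution puts weight on tables with events in G1, which the outcome definition rules out. The null of equal rates can be true only if the cells cause no events at all.

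**4. Chance of a significant result.** With G1 fixed at zero, the test rejects when G2 has 8 or more events, so the probability is P(X ≥ 8) for X ~ Binomial(72, r).

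| Assumed true G2 rate r | P(significant) |
|---|---|
| 5% | 2.7% |
| 10% | 43% |
| 15% | 86% |
| 20% | 98% |

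At a true cell-related rate of 5%, the test would almost always be non-significant.

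**5. The same data without a test.** Reported as an incidence, 7/72 is 9.7% with an exact 95% CI of 4.0% to 19.0%. Zero events in 72 would give an upper exact 95% limit of 1 − 0.025^(1/72) = 5.0%. Either statement is informative, and neither needs G1.

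**6. The test with the restriction removed.** If events are counted alike in both arms and true rates are equal, Fisher's test at 36 and 72 rejects in 3.2% of trials at a 10% rate and in 3.5% at a 20% rate. It is then a valid, somewhat conservative test.

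**7. Which other rows cover the gap.** SO6 compares complications with no cell-related restriction. SAEs are named only in SO7. No row compares SAEs irrespective of cause.

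**The case against.** The strongest objection is that SO6 already does most of the work. Its list is broad, covers both arms and includes marrow and autograft harvest. A serious harvest event in either arm would be counted there, although not tabulated by seriousness. This stands. A reader might infer from SO7 that the trial's whole safety comparison is void, or that serious harvest events are never set against events in the cell arms. The article does not support either inference.

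Second, the qualifier in "Safety understood as early or global complication rates and SAE rates, related to the use of hBM-MSCs" may attach to SAE rates alone. That is a fair reading. The complication half would then repeat SO6 with a valid comparator, but the SAE half would still be zero by definition in G1.

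Third, the 8/72 threshold reflects sample size. This also stands. A comparison of all SAEs with a non-zero G1 rate would need a larger absolute excess in G2, so the remedy buys a meaningful contrast and no added sensitivity. Nor may one say that a true 10% rate would be missed: the test rejects in about 43% of such trials.

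Fourth, open-label attribution is not established as a bias. Section 2.3 has three independent clinicians adjudicate the primary and other clinical outcomes on blinded files, although the article does not say whether SAE causality is included. Blinding would not remove the structural zero in any case.

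Finally, because the mFAS is the "modified full analysis set (mFAS) that will include all patients who have received treatment", a reader might infer that harms in patients who had marrow harvested but were never implanted are lost. The article does not say so, and a condensed article may leave the safety population to the full protocol or SAP.

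**Conclusion.** The point holds for SO7, and within SO7 for SAEs on either reading of the sentence. As worded, the G1 rate is zero by construction, the test can only count against G2, and non-significance (any G2 count up to 7/72) is no evidence of comparable safety. The consequence is that Table 1 contains no valid G1 versus G2 comparison of SAEs.

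This rests on G1 patients being treated as allocated and on Table 1 being applied as written. It does not depend on the assumed 5% to 20% rates, which only illustrate how the test behaves. SO7 is one secondary objective with no stated power, so the primary inference is unaffected, and the comparison of complications under SO6 stands. The issue still deserves correction, because SO7 is the only row that names SAEs in a trial that Section 4 calls phase III.

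**What to change.** 1. Redefine the SO7 contrast of G1 with G2 as all SAEs irrespective of attributed cause, at 6, 12 and 24 months, reported as a risk difference with 95% CI. Fisher's test may be kept beside it.
2. Leave complications under SO6, so that the two rows do not overlap.
3. Report hBM-MSC-related events as incidence in G2a and in G2b, each with an exact 95% CI, and do not test them against G1.

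The cost is a change of wording in the SO7 row of Table 1 and in Section 2.2, with matching text in the SAP. No extra patients or visits are needed. I assume that SAEs are recorded in all three arms whatever their cause.

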## Abstract

ORTHOUNION is a multicentre, open, comparative, three-arm, randomized clinical trial (EudraCT number 2015-000431-32) to compare the efficacy, at one and two years, of autologous human bone marrow-derived expanded mesenchymal stromal cell (hBM-MSC) treatments versus iliac crest autograft (ICA) to enhance bone healing in patients with diaphyseal and/or metaphysodiaphyseal fracture (femur, tibia, and humerus) status of atrophic or oligotrophic nonunion (more than 9 months after the acute fracture, including recalcitrant cases after failed treatments). The primary objective is to determine if the treatment with hBM-MSCs combined with biomaterial is superior to ICA in obtaining bone healing. If confirmed, a secondary objective is set to determine if the dose of 100 × 10^6^ hBM-MSCs is noninferior to that of 200 × 10^6^ hBM-MSCs. The participants (*n* = 108) will be randomly assigned to either the experimental low dose (*n* = 36), the experimental high dose (*n* = 36), or the comparator arm (*n* = 36) using a central randomization service. The trial will be conducted in 20 clinical centres in Spain, France, Germany, and Italy under the same clinical protocol. The confirmation of superiority for the proposed ATMP in nonunions may foster the future of bone regenerative medicine in this indication. On the contrary, absence of superiority may underline its limitations in clinical use.

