## 3. Statistical Analysis

### 3.1. Sample Size

#### 3.1.1. Test of Superiority (Primary Endpoint) for G1 versus G2 Comparison

For an allocation 1 : 2 to test the percentage of bone consolidation between G1 and G2, the sample size of 36 in comparator arm (ICA) and 72 in experimental arm (hBM-MSC) achieve more than 80% power to detect superiority with a clinically meaningful margin of superiority of 20%, considering a 5% loss. Despite the uncertainties derived from the fact that no head-to-head comparisons have been tested in well-designed randomized clinical trials, literature data suggest that the control arm (G1) may have a rate of 74% in efficacy [8] and that it is reasonable to expect 20% superiority for the rate of responders in the experimental arm (G2a + G2b) [21, 22]. The significance level of the test will be established at the 2.5% one-sided alpha level (equivalent to 5% two-sided alpha level).

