## 4. Discussion

There is a lack of multicentric, randomized clinical trials in the literature, capable of defining the value of current regenerative medicine strategies based on MSCs. Bone healing in difficult clinical settings has gathered multiple early trials with cell therapy, but the available evidence is limited.

Nonunions after long bone fractures are a challenging scenario to evaluate the efficacy of cell therapy or other competing technologies. Furthermore, the severity of the included cases may impact the results. Delayed unions of the tibia were healed by bone marrow MSCs and platelet-rich plasma [25], but obviously the severity of the cases was limited. Clinical trials on the treatment of long nonunions frequently include any type of nonunion, from hypertrophic to oligotrophic or atrophic, and the results may be impacted by the case mix. A reference multicentric trial [8] included 25% atrophic nonunions in the control arm versus 42% in the experimental arm. To solve this issue, our trial will exclude hypertrophic nonunions.

The control arm in comparative trials about bone healing is a difficult choice. Although iliac crest autograft has long been considered the standard augmentation to obtain bone healing, this control may be variable due to the patient and the surgical variability. Besides, no reference studies are available about the effectiveness of ICA to support bone healing in nonunions. Recent data can only be obtained from its use as controls in other studies [8, 26], but the variability in the obtention of ICA and the subsequent complications [7, 27, 28] foster the proposal of alternatives. We used this information to quantitatively estimate the expected healing rates with ICA, although it may vary depending on the type and location of the nonunion.

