SO: secondary objective; NRS: Numeric Rating Scale; AE: adverse event. ^∗^Cortical value: 1 point if fracture is unchanged, 2 points if callus is noncontinuous, 3 points if callus is continuous but fracture is still apparent, 4 points if callus is with same density as cortical, and 0 points if noninterpretable or nonvisible. ^∗∗^Variables of interest: manufacturing centre (nominal), anatomical site of the fracture (femur, humerus, and tibia), sex (male, female), smoking habit (yes, no), and time since acute fracture (months).

**Table 2 tab2:** ORTHOUNION clinical trial inclusion/exclusion criteria.

*Inclusion criteria*
(1) Age 18 to 65, both sexes (2) Traumatic isolated closed or open Gustilo I and II, IIIA and IIIB humerus, tibial or femur diaphyseal, or metaphysodiaphyseal fracture with a status of atrophic, oligotrophic, or normotrophic nonunion. A nonunion is defined as a fracture not healed at least 9 months after the originating trauma that meets the following criteria: (i) Insufficient bone bridging to stabilize the fracture (ii) Insufficient bone biological activity in the fracture (iii) Failure of previous treatment (including bone grafting) (3) At least 9 months from acute fracture (4) Able to understand, accept, and sign informed consent (5) Medical health coverage (6) Able to understand and accept the study constraints
*Exclusion criteria*

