(1) Hypertrophic nonunions (2) Segmental bone loss requiring specific therapy (bone transport, vascularized graft, large structural allograft, megaprosthesis, etc.) (3) Unrecovered vascular or neural injury (4) Other fractures causing interference with weight bearing (5) Visceral injuries or diseases interfering with callus formation (severe cranioencephalic trauma, etc.) (6) Active infection of any location and aetiology (7) Surgical contraindication of any cause (8) Pregnancy, breast-feeding women, and women who are of childbearing age and not practicing adequate birth control. The following methods are considered adequate: (i) Combined hormonal contraception (ii) Injected hormonal contraception (iii) Implanted hormonal contraception (iv) Progesterone-only hormonal contraception associated with inhibition of ovulation (v) Placement of an intrauterine device (IUD) (vi) Placement of intrauterine hormone-releasing system (IUS) (9) Malignant tumour (past history or concurrent disease) (except carcinoma in situ or basalioma in remission) (10) History of bone harvesting on iliac crest contraindicating new iliac crest bone graft harvesting or bone marrow collection (11) Insulin-dependent diabetes (12) Any evidence (confirmed by PCR) of active infection with HIV, hepatitis B, or hepatitis C (13) Any evidence of syphilis (14) Known allergies to products involved in the production process of MSC (15) Corticoid or immunosuppressive therapy more than one week in three months prior to study inclusion (16) Autoimmune inflammatory disease (17) Current treatment by bisphosphonates not stopped three months prior to study inclusion (18) Impossibility to meet at the appointments for the follow-up (19) Participation in another therapeutic trial in the previous 3 months (20) Second nonunion in case of bilateral or multiple nonunions (only one nonunion per patient will be included in the trial)

**Table 3 tab3:** ORTHOUNION arms of treatment description.

Study arm	Treatment	Dosage	Administration
G1: ICA (active comparator arm)	Iliac crest autograft	10 cc	Local administration under surgical procedure of nonunions
G2A: high dose of BM-MSC + B (experimental arm)	Expanded bone marrow mesenchymal stem cells, plus biomaterial (MBCP+)	200 × 10^6^ cells in 10 cc of biomaterial	
G2B: low dose of BM-MSC + B (experimental arm)		100 × 10^6^ cells in 10 cc of biomaterial

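### Table 2 admits normotrophic nonunions, but the abstract and primary objective name only atrophic or oligotrophic ones

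*Protocol article*

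**What the plan says.** The protocol article describes the target population in several places.

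- **Abstract:** fractures with "status of atrophic or oligotrophic nonunion".
- **Section 2.2, primary objective:** "atrophic or oligotrophic nonunions after a fracture", followed by three conditions on bridging, biological activity and failed previous treatment.
- **Table 2, inclusion criterion 2:** a fracture "with a status of atrophic, oligotrophic, or normotrophic nonunion", followed by the same three conditions, among them "Insufficient bone biological activity in the fracture".
- **Table 2, exclusion criterion 1:** "Hypertrophic nonunions". No other nonunion type is excluded.
- **Section 4, Discussion:** in trials that mix nonunion types, "the results may be impacted by the case mix". The remedy given for this trial is to exclude hypertrophic cases.

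Section 3.2 defines the modified full analysis set as all treated patients, and the per protocol set as those among them without major deviations.

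**The concern.** The objective says which patients the answer is about, and the eligibility table decides who is enrolled. Here they disagree on a whole class of nonunion. A site applying Table 2 correctly could randomise a normotrophic case, while a reader of the abstract or objective would believe that no such case was in the trial.

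Two things are at stake. The first is the indication to which a result applies: a superiority claim for atrophic or oligotrophic nonunion would rest partly on patients of another type. The second is consistency between sites. With 20 sites in four countries, some may go by the objective and others by the table, so the enrolled mix could vary from site to site for no clinical reason.

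**Working it through.** **Step 1. Nonunion types named in each place**

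| Place | Atrophic | Oligotrophic | Normotrophic | Hypertrophic |
|---|---|---|---|---|
| Abstract | in | in | not named | not named |
| Section 2.2, primary objective | in | in | not named | not named |
| Table 2, inclusion 2 | in | in | **in** | not named |
| Table 2, exclusion 1 | – | – | not excluded | out |
| Section 4 | – | – | not addressed | out |

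The only conflict is the normotrophic column. The exclusion list and the Discussion do not resolve it, since both deal only with hypertrophic cases.

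**Step 2. Do the shared conditions remove the conflict?** The three conditions stand in both the objective and inclusion criterion 2, so they narrow both populations alike. They may limit which normotrophic cases qualify. They do not exclude the class, because the same criterion lists it as eligible.

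**Step 3. Would the analysis sets remove such patients?** A treated normotrophic patient belongs to the modified full analysis set by definition. That patient also satisfies Table 2, so nonunion type alone would not be a protocol deviation, and the per protocol set would keep the patient too.

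**Step 4. Could the described analyses separate them?**
- Primary model (Table 1): treatment, manufacturing site and baseline REBORNE value.
- Declared subgroups (section 3.2): manufacturing site, anatomical site, time since fracture, smoking and sex.
- Factors of interest (Table 1 footnote): the same five.

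Nonunion type is in none of these lists.

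**Step 5. Does a power consequence follow?** The plan's own figure comes first. The inputs from section 3.1.1 are 36 versus 72 patients, 74% versus 94% (reading the 20% as absolute points) and one-sided 2.5%. With a pooled-variance normal test:

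- Pooled rate = (36 × 0.74 + 72 × 0.94)/108 = 0.8733
- Null SE = √[0.8733 × 0.1267 × (1/36 + 1/72)] = 0.0679
- Alternative SE = √[0.74 × 0.26/36 + 0.94 × 0.06/72] = 0.0783
- Power = Φ[(0.20 − 1.96 × 0.0679)/0.0783] = Φ(0.855) = 80.4%

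This reproduces the stated figure of more than 80% before losses. With 34 versus 68 after the 5% loss it is 78.3%.

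Next, suppose that 30% of patients are normotrophic and the other 70% follow 74% versus 94%. Every normotrophic input below is an assumption, because the article gives none.

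| Normotrophic healing, autograft / cells | Overall control rate | Overall cell rate | Power, 36 vs 72 |
|---|---|---|---|
| 74% / 94% | 74.0% | 94.0% | 80.4% |
| 80% / 94% | 75.8% | 94.0% | 75.0% |
| 90% / 94% | 78.8% | 94.0% | 64.0% |
| 80% / 100% | 75.8% | 95.8% | 84.2% |

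For example, the control rate in the second row is 0.70 × 0.74 + 0.30 × 0.80 = 0.758. Power falls, holds or rises according to inputs on which the documents are silent.

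**The case against.** The strongest defence is that the operative definition is shared. Whatever the label, every enrolled nonunion must show insufficient bridging, insufficient biological activity and failed previous treatment, and the objective repeats these conditions. The Introduction links these features to atrophic nonunion, so few true normotrophic cases might qualify. This has weight: it may keep the discrepancy small in practice. It does not settle the matter, because Table 2 names the class as eligible and the objective does not.

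A second defence is that a journal article condenses the full protocol. That does not apply here, since the article prints both the objective and the eligibility criteria, and they disagree.

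A reader might also infer that normotrophic cases heal better on autograft, push the control rate above the planned figure and leave too little room for a 20-point gain. The documents do not support this. They give no healing rate or share for the class. The planning assumption that "the control arm (G1) may have a rate of 74% in efficacy" comes from 45 of 61 autograft controls of whom only 25% had atrophic nonunions (section 1), so it already reflects a mixed group and is not a pure atrophic or oligotrophic rate. Removing one word from Table 2 would not align eligibility with that figure either.

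**Conclusion.** The contradiction stands, and it rests on wording alone: the eligibility table admits a nonunion type that the abstract and primary objective do not name, without explanation. Patients of that type would be analysed with the rest, and the analyses described in the article could not show their influence.

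Its size is unknown. It depends on how many normotrophic cases meet the three further conditions, and the article gives no figure. If there are none, nothing changes; if there are many, the result belongs to a wider population than the one declared.

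No effect on power is established, in size or in direction, and the mismatch is not an error in the sample size calculation. It would also go too far to say that the result could not be interpreted for the declared indication, since the biological and treatment-failure conditions are common to both descriptions. This is an inconsistency that should be corrected, not a flaw that undermines the design.

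**What to change.** Reconcile the abstract, section 2.2 and inclusion criterion 2 so that all three name the same nonunion types. The choice of population is for the investigators.

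- **If the population is atrophic and oligotrophic only:** bring Table 2 into line with the objective. The cost is a one-word amendment and a notice to sites, with a possible small effect on recruitment.
- **If normotrophic cases remain eligible:** name them in the abstract and objective, state the conclusion for that wider population, and add nonunion type to the subgroups in section 3.2 or the factors of interest under Table 1. The cost is an amendment to the objective and one more exploratory factor. Type already has to be judged at screening to apply Table 2, so little extra data should be needed.

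Either change is best made early. Section 5 reports that the German and Italian evaluations were still under way, so sites there could open with consistent wording, while France and Spain would need an amendment to an authorised protocol.
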